##### **2. Dry Eyes Assessments**

Dry eyes condition is assessed using several modalities, which are OSDI (Ocular Surface Disease Index) questionnaire, Tear Break-up Time (TBUT), Schirmer Test with anesthesia and without anesthesia.

##### **2.1. Ocular Surface Disease Index (OSDI) Questionnaire**

Subjective symptoms of dry eyes are assessed using OSDI questionnaire that consists of 12 questions regarding dry eyes symptoms. Each question answered with 0-4 Likert scale (0: never, 1: seldom, 2: sometimes, 3: often, 4: always). Final score is calculated with:  $(\text{total score} \times 100) / (\text{total questions answered} \times 4)$ . Final score then categorized into: normal (0-12), mild dry eye (13-22), moderate dry eye (23-32), or severe dry eye (33-100).

##### **2.2. Tear Break-up Time (TBUT)**

TBUT is measured with putting a fluorescent paper strip on bulbar conjunctiva and ask subject to blink. Then examine eye using cobalt blue light with a slit lamp, while subject holds eye open. The duration between eyelid opens and appearance of dry spot on corneal surface is the tear film break-up time, and measured in seconds. TBUT less than 10 seconds shows tear film instability.

##### **2.3. Schirmer Test**

Schirmer test aims to assess tear film secretion. This test using Whatman filter paper that put in lower lid fornix at third lateral side, and subject closes eyes for 5 minutes. Wet part of the filter paper then measured in millimeters to determine the result. Schirmer test is done in two ways: without

anesthesia and with anesthesia before putting the paper in the fornix. In normal eyes, wet part of the Whatman paper reaches 10 millimeters after 5 minutes.

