Lagophthalmos pathogenesis started when *M. leprae* invade peripheral nerve (Schwann cell) where there were protein bridging to Schwann cell cytoskeleton, which are laminin-2,  $\alpha$ -dystroglycan,  $\beta$ -dystroglycan, and dystrophin. *M. leprae* would enter Schwann cell endoneurium, and then stimulate inflammation response in nerve cells. Invaded nerve cells are facial cranial nerve (CN VII) zygomatic and temporal branches, which leads to orbicularis oculi muscle paralysis so that eyelid could not close completely (paralytic lagophthalmos), also ophthalmic branch of trigeminal cranial nerve (CN V) which leads to decrease in corneal sensibility. Paralytic lagophthalmos with decreased corneal sensibility could cause corneal opacity and decreased visual acuity that leads to blindness (Lewallen & Courtright 2012; Sjamsoe & Sjamsoe-Daili 2003; Grzybowski et al 2015; Ebenezer 2016).

Corneal opacity due to lagophthalmos was the most common cause of blindness in leprosy (Lewallen et al. 2000).

Lagophthalmos management depends on duration and size of lagophthalmos, also the presence of corneal exposure. In lagophthalmos with eyelid gap  $>6$  mm, presence of corneal exposure, and duration  $>6$  months, the ideal treatment is with eyelid reconstruction surgery (Hogeweg 2010). There were several reconstruction surgery techniques for lagophthalmos, although these techniques gave various results. The easiest surgery technique to manage lagophthalmos is permanent lateral tarsorrhaphy, which was done with joining upper and lower lateral side of the eyelid so that patient could still see from the central side. Even though, this technique has its limitation, which is limited temporal visual field and poor cosmetic result (Hogeweg 2001; Hogeweg 2010; Rajak et al. 2015).

Therefore, this study attempts to combine tarsorrhaphy technique with another eyelid reconstruction techniques, which are levator recess and canthopexy. Levator recess technique aims to weaken levator muscle to enable eyelid closure passively, while canthopexy aims to tighten lower eyelid, because in lagophthalmos due to orbicularis paralysis, there were tendency of lower lid laxity.

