#### **c. Interventions**

##### Modified Tarsorrhaphy Technique

1. Patient preparation and aseptic procedures on subject eye
2. Marking at eyelid crease skin
3. Subcutaneous anesthesia using Lidocain HCl 20 mg and Epinephrine 0.0125 mg/ml (Pehacain(R)) on upper eyelid and lateral side of the eye
4. Incision at skin crease and dissection of orbicularis muscle to clean superior tarsal border
5. Levator recess procedure with local anesthesia injection at conjunctiva to separate levator aponeurosis from conjunctiva. Open orbital septum at the level of superior tarsal. Excision of levator aponeurosis at its insertion site in the tarsal. Separate aponeurosis levator from conjunctiva as far as possible
6. Do canthotomy and lateral cantholysis. Excision of upper and lower eyelid margin as long as 10 mm from lateral canthal to central. Lateral tarsorrhaphy suture using polyglactin 6-0 with reverse cutting needle
7. Do canthopexy/lateral tarsal strip (LTS) using polyglactin 5-0 with reverse cutting needle and canthoplasty using polyglactin 6-0 with reverse cutting needle
8. Suture skin to form lid crease (skin-tarsal-skin) at 3 points and suture skin in between using polypropylene 6-0 with reverse cutting needle.

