### Gold Weight Implant Technique

1. Patient preparation and aseptic procedures on subject eye
2. Marking at eyelid crease skin
3. Subcutaneous anesthesia using Lidocain HCl 20 mg and Epinephrine 0.0125 mg/ml (Pehacain(R)) on upper eyelid and lateral side of the eye
4. Incision at skin crease and dissection of orbicularis muscle to clean superior tarsal border
5. Open orbital septum at middle border of superior tarsal
6. Eversion of upper eyelid, do subconjunctiva anesthesia to separate aponeurosis from conjunctiva
7. Levator recess procedure with excision of levator aponeurosis at its insertion site in the tarsal. Separate aponeurosis levator from conjunctiva
8. Implant placed at superior tarsal border underneath levator recess with attachment to septal frill, and then fixed at tarsal using polypropilene 6-0 with reverse cutting needle.
9. Suture orbicularis muscle to cover implant using polyglactin 6-0 with reverse cutting needle and suture skinn using polypropilene 6-0 with reverse cutting needle.

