## e. Participant Timeline

### Time Schedule

Lagophthalmos distance and dry eyes assessments (OSDI questionnaire, TBUT, Schirmer test without anesthesia, Schirmer test with anesthesia), epitheliopathy, corneal sensibility, and corneal exposure will be assessed at 1 day, 7 days, 1 month, 3 months, and 1 year post-operatively. Complication and cost of surgery will be assessed intra-operative and post-operative until 1 year. Duration of surgery will be assessed during the surgery.

[figure not shown]

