### OCULAR SURFACE DISEASE INDEX

| Have you experienced any of the following during the last week?                                          | All of the time | Most of the time | Half of the time | Some of the time | None of the time |
|----------------------------------------------------------------------------------------------------------|-----------------|------------------|------------------|------------------|------------------|
| A. Eyes that are sensitive to light?                                                                     | 4               | 3                | 2                | 1                | 0                |
| B. Eyes that feel gritty?                                                                                | 4               | 3                | 2                | 1                | 0                |
| C. Painful or sore eyes?                                                                                 | 4               | 3                | 2                | 1                | 0                |
| D. Blurred vision?                                                                                       | 4               | 3                | 2                | 1                | 0                |
| E. Poor vision?                                                                                          | 4               | 3                | 2                | 1                | 0                |
| Have problems with your eyes limited you in performing any of the following during the last week? |                 |                  |                  |                  |                  |
| F. Reading?                                                                                              | 4               | 3                | 2                | 1                | 0                |
| G. Driving at night?                                                                                     | 4               | 3                | 2                | 1                | 0                |
| H. Working with a computer or bank machine (ATM)?                                                        | 4               | 3                | 2                | 1                | 0                |
| I. Watching TV?                                                                                          | 4               | 3                | 2                | 1                | 0                |

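### The Schirmer strip site is closed by surgery in the tarsorrhaphy arm only, and the day-1 OSDI recalls a week that is about 6/7 pre-operative

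*Protocol*

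**What the plan says.** **Schirmer.** Protocol section 2.d (2.3 Schirmer Test) states the purpose, "Schirmer test aims to assess tear film secretion", and gives one placement for all eyes: "Whatman filter paper that put in lower lid fornix at third lateral side". The test is done with and without anesthesia, which makes two outcomes. The readable text gives no separate instruction by arm or for visits after surgery.

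**Surgery.** In section 2.c, step 6 of the Modified Tarsorrhaphy Technique reads "Excision of upper and lower eyelid margin as long as 10 mm from lateral canthal to central", followed by "Lateral tarsorrhaphy suture using polyglactin 6-0 with reverse cutting needle". Section 1.a describes permanent lateral tarsorrhaphy in the same sense: "joining upper and lower lateral side of the eyelid so that patient could still see from the central side". In the other arm the weight goes on the upper lid ("Implant placed at superior tarsal border underneath levator recess"), and no step joins the lid margins.

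**OSDI.** The Appendix 6 form opens with "Have you experienced any of the following during the last week", and its other two blocks of items use the same one-week window. Under Time Schedule (section 2.e), OSDI and both Schirmer tests, with the other eye assessments, "will be assessed at 1 day, 7 days, 1 month, 3 months, and 1 year post-operatively".

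**The concern.** A between-arm comparison needs the same measurement in both arms. Here one of the two operations closes the part of the lid at which the Schirmer strip is to be placed. The assessor must use another position in that arm, so treatment decides the measuring site. A Schirmer difference between arms, or a change from before to after surgery within the tarsorrhaphy arm, could come from tear secretion, from strip position or from both, and the data could not separate them. Three surgeons measure the outcomes, and the readable text does not stop each from choosing a different substitute position.

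The OSDI problem is of another kind. A questionnaire with a one-week window, given one day after surgery, asks mostly about days before surgery. Labelling that score post-operative understates any early change in symptoms.

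**Working it through.** The protocol prints no figure of its own on either point, so there is none to reproduce. Its sample size does not enter.

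**Schirmer: how far the closed segment overlaps the strip site**

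Inputs: closure of 10 mm from the lateral canthus (section 2.c, step 6); strip in the lateral third (section 2.d, 2.3). The length of the lid opening, L, is not in the document; 24 to 34 mm is assumed.

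Both segments start at the lateral canthus, so they overlap whatever L is. L decides only how much of the site is covered:

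- lateral third = L / 3
- share covered = min(1, 10 / (L / 3))

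| L (mm, assumed) | Lateral third (mm) | Share covered by 10 mm |
|---|---|---|
| 24 | 8.0 | 100% |
| 28 | 9.3 | 100% |
| 30 | 10.0 | 100% |
| 32 | 10.7 | 94% |
| 34 | 11.3 | 88% |

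The most that stays open is 11.3 − 10 = 1.3 mm, at L = 34 mm.

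The placement can also be read as the lateral third of whatever opening is left. That site runs from 10 mm to 10 + (L − 10) / 3 mm from the original canthus:

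- L = 24: 10 to 10 + 14/3 = 14.7 mm
- L = 34: 10 to 10 + 24/3 = 18.0 mm

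In the gold weight arm it still runs from 0 to L / 3, that is 0 to 8.0 mm or 0 to 11.3 mm. For L up to 30 mm the two sites do not overlap; at 34 mm they share 1.3 mm. Both readings give a site that differs between arms and that moves after surgery in one arm only.

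Scope: 2 Schirmer outcomes × 5 post-operative visits.

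**OSDI: share of the recall week before surgery**

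Inputs: a 7-day window (Appendix 6); visits at day 1, day 7, 1 month, 3 months and 1 year (section 2.e). With d the days since surgery, the pre-operative share is max(0, 7 − d) / 7.

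- Day 1: (7 − 1) / 7 = 6/7 = 86%
- Day 7: (7 − 7) / 7 = 0%
- 1 month, 3 months, 1 year: 0%

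If symptoms changed at once and answers weighted the week evenly (both assumptions), the day-1 score would show 1/7 = 14% of the change.

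**The case against.** **The strip can go elsewhere.** The placement text gives no millimetre position, the fornix itself is not excised, and an opening remains, so Schirmer is still feasible after tarsorrhaphy. Step 7 (canthopexy or lateral tarsal strip, with canthoplasty) also alters the lateral canthus, so coverage worked out on an unoperated lid is approximate. All of this stands. It rules out the reading that Schirmer cannot register an effect of the operation, but it leaves a site that depends on the arm.

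**No bias is demonstrated.** Correct. Nothing in the document says how many millimetres of wetting a change of position is worth. The finding is lost comparability; neither the direction nor the size of an error is known.

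**The arm-specific forms cannot be read.** Appendices 4 and 5 are illegible in the text at hand, and the timeline figure is not shown. They might state a strip site. An arm-specific site would confirm the difference. A common site would depart from section 2.d, and the two would still need reconciling. Nor does the readable schedule list a pre-operative Schirmer explicitly; the pre/post argument applies if one is taken, while the between-arm argument does not need it.

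**The OSDI point is small.** The window is the same in both randomised arms, so it favours neither, and only one of five visits is affected. This is accepted. A reader might go further and infer that the averaged OSDI effect is diluted by (6/7) × (1/5) = 17%. The document does not support that. Statistical Methods names a repeated-measures general linear model but not the outcomes, visits or contrast it uses. The figure would also need equal visit weights, evenly weighted recall and an immediate, constant effect.

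**Conclusion.** The point holds in two limited parts.

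First, the Schirmer placement and step 6 of the modified tarsorrhaphy cannot both be followed as written after surgery, and only one arm is affected. Between-arm and pre/post Schirmer comparisons, with and without anesthesia, therefore mix strip position with tear secretion. That the two segments overlap follows from the text; the 88 to 100% coverage rests on the assumed 24 to 34 mm opening and an unoperated lid. The effect on the readings is unknown.

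Second, the day-1 OSDI is a diluted value, about 86% pre-operative in its recall window, and not a true post-operative one. The other four OSDI visits are unaffected.

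It would be too strong to say that either outcome cannot reflect the operation: a strip can still be placed in the remaining opening, and day 1 still includes about one post-operative day. The sample size and the lagophthalmos comparison do not change. Correction is still worthwhile before data are collected, because no later analysis can recover a common strip site that was never used.

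**What to change.** 1. Reconcile section 2.d (2.3 Schirmer Test) with step 6 of the Modified Tarsorrhaphy Technique by changing the measurement instruction; the surgical step is not in question here. Name one strip site that stays accessible in both arms, for the investigators to choose, and require it before surgery and at every visit, with and without anesthesia. Make the post-operative forms in Appendices 4 and 5 agree with it.
2. In section 2.e, drop OSDI from the day-1 assessments, or keep it but state that it is not analysed as a post-operative value. Day 7 is then the first post-operative OSDI.

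The cost is two wording changes. Readings at a new site will be less comparable with lateral-third Schirmer values elsewhere, and OSDI loses one time point. Neither change touches treatment or the number of eyes.

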### 3. Epitheliopathy

Epitheliopathy is examined with fluorescent staining with cobalt blue light using slit lamp. Epitheliopathy is measured with the presence of epitheliopathy or no epitheliopathy.

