Another common technique to reconstruct CN VII paralysis as lagophthalmos management is upper eyelid loading, using gold weight implant (Rahman & Sadiq 2007). Gold weight implant has a high success rate as lagophthalmos treatment. This technique uses gold implant and attach it into the upper eyelid so that the weight of the gold pulled by the gravity and the eyelid closes passively when palpebral levator muscle relaxed. The advantages of this technique are: increasing eyelid closure with gravity pull, protecting cornea from exposure, and good cosmetic result. The disadvantages of gold weight implant technique are: expensive material, risk of complications, such as inflammation, allergic reaction, extrusion, migration, and astigmatism (Bladen et al 2012; Chi 2016). Wagh et al (2016) showed gold weight implant as the most effective treatment for paralytic lagophthalmos from keratopathy improvement and decrease in ocular surface defects.

Generally, eye disorders in leprosy patients were poorly diagnosed in primary health facility. Ocular manifestations in leprosy were assessed by general physician, dermatovenereology specialist, and ophthalmologist with different level of knowledge so that ocular complication in leprosy may still be underdiagnosed (Ebenezer 2016). Every eye disorders in leprosy patients, including lagophthalmos, need early detection and early treatment to prevent blindness. Eyelid reconstruction surgery is needed to correct paralytic lagophthalmos in leprosy patients, but not all health facility has a trained ophthalmologist to

do eyelid reconstruction surgery. Limited access and cost for treatment in tertiary health facility, leprosy patients commonly came when ocular complications have reached severe visual impairment. Therefore, this study is useful in ophthalmology field for several reasons:

1. There were no studies comparing effectivity and efficiency of various reconstruction surgery techniques for lagophthalmos in leprosy patients.
2. There were no complete data in Indonesia regarding incidence and prevalence of lagophthalmos due to leprosy.
3. With this research, better leprosy management can be carried out to prevent blindness from lagophthalmos in leprosy patients.

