#### **f. Sample Size**

This study uses sample size calculation formula for two-tailed hypothesis test:

$$n = \frac{Sd^2 (Z_{1-\alpha/2} + Z_{1-\beta})^2}{(\mu_0 - \mu_a)^2}$$

$$n = 1,19^2 \frac{(1,96 + 0,842)^2}{1^2}$$
$$n = 12$$

n = total sample

Sd = standard deviation of mean difference (1.19)

$Z_{1-\alpha/2}$  = type 1 error (1.96)

$Z_{1-\beta}$  = type 2 error (0.842)

$\mu_0 - \mu_a$  = significant mean difference of both groups (1 mm represents significant)

Researcher determines sample size of minimum 12 eyes in each group.

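### Epitheliopathy is recorded only as present or absent, so any change in staining short of complete clearance is lost at data capture; an ordinal grade from the same examination would keep it.

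*Protocol*

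**What the plan says.** Under Outcomes, item 3 (Epitheliopathy), the protocol describes the examination: "Epitheliopathy is examined with fluorescent staining with cobalt blue light using slit lamp". It then defines the outcome: "Epitheliopathy is measured with the presence of epitheliopathy or no epitheliopathy". No grade, score or area is given.

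Epitheliopathy is specific objective c and one of five effectivity outcomes. The others are lagophthalmos distance (mm), dry-eye tests (OSDI score, TBUT in seconds, Schirmer in mm), corneal sensibility (mm, in five categories) and corneal exposure (mm). Epitheliopathy is the only one with a two-level scale.

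The Background cites evidence for the comparator in terms of the corneal surface. One cited study is said to show "gold weight implant as the most effective treatment for paralytic lagophthalmos from keratopathy improvement and decrease in ocular surface defects".

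The Sample Size section derives its number from a 1 mm mean difference and concludes: "Researcher determines sample size of minimum 12 eyes in each group". The Recruitment section adds 20% for drop-out. No epitheliopathy rate appears anywhere in the protocol.

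**The concern.** A two-level scale registers only two events: a stained cornea that clears fully, or a clear cornea that starts to stain. Dense staining that fades to a trace, or a trace that becomes dense, is present on both occasions and so unchanged. The assessor sees the amount of staining but has nowhere in the outcome definition to put it.

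This matters because the Background runs from exposure and reduced corneal sensibility to opacity and blindness, and gives prevention of blindness as a reason for the trial. The other effectivity outcomes measure gaps, tears, symptoms or touch threshold; none measures surface damage. The benefit cited for the gold weight is an improvement and a decrease, which are matters of degree. The loss occurs at data capture, so a statistical analysis plan cannot repair it.

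**Working it through.** **1. The plan's own figure.** Inputs from Sample Size: SD 1.19, difference 1 mm, z-values 1.96 and 0.842.

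n = 1.19² × (1.96 + 0.842)² / 1² = 1.4161 × 7.8512 = 11.12, rounded up to 12. The stated 12 reproduces from the formula printed there. It rests on a distance, not on an epitheliopathy rate. With the 20% addition, 12 × 1.2 = 14.4, so about 15 per arm. Whether the formula suits two independent groups is a separate matter and is not used here.

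**2. What a yes/no comparison can show at 12 v 12.** The protocol does not assign a test to this outcome; two-sided Fisher's exact test at 0.05 is used here, treating eyes as independent.

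- 0 v 4 eyes: p = 0.093; 0 v 5: p = 0.037.
- 2 v 7 eyes: p = 0.089; 2 v 8: p = 0.036.
- Over the whole range, the smallest significant splits are 5 v 0, 7 v 1, 8 v 2, 9 v 3, 10 v 4, 11 v 5 and 12 v 7.

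The gap needed is 5 to 6 eyes: 5/12 = 42 points to 6/12 = 50 points.

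**3. Power for present/absent.** The rates are assumptions, because the protocol gives none. Exact Fisher power at 12 per arm:

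| True rates | Power |
|---|---|
| 80% v 60% | 9% |
| 80% v 50% | 21% |
| 80% v 40% | 39% |
| 80% v 30% | 61% |
| 80% v 20% | 81% |

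For 80% power the true gap must be about 56 to 60 points (about 52 to 55 by the pooled z-test). With 15 per arm and no losses it is still about 53 to 56 points by Fisher, and 80% v 50% has only 25% power.

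**4. What a grade would add.** Four assumed grades from none to dense, 12 eyes per arm. Fisher is applied to any staining, and a simulated Mann-Whitney test to the grade. Repeat simulations move the figures by a point or two.

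| Arm 1 (%) | Arm 2 (%) | Any staining | Fisher | Mann-Whitney |
|---|---|---|---|---|
| 50/20/20/10 | 20/40/30/10 | 50% v 80% | 21% | 20% |
| 70/20/5/5 | 20/60/10/10 | 30% v 80% | 61% | 61% |
| 40/30/20/10 | 20/30/30/20 | 60% v 80% | 9% | 19% |
| 40/40/15/5 | 20/20/30/30 | 60% v 80% | 9% | 47% |
| 30/10/20/40 | 30/50/15/5 | 70% v 70% | 2% | 31% |

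In the first two rows the arms differ mainly in whether staining is absent, and the grade adds nothing. In the last two they differ strongly in how heavily stained eyes stain, and the grade adds a great deal. In the last row, where presence is equal, the yes/no scale cannot see the difference at all. At 15 per arm the fourth row becomes 11% v 58%.

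**The case against.** The strongest reply is that this is one of several outcomes, that the trial is sized on a distance, and that the gain from grading depends wholly on a pattern the documents do not describe. Most of that stands. No primary outcome is named, and the first two rows of the table show that present/absent loses nothing if the techniques differ in whether staining clears. The need for a gap of 5 to 6 eyes is mainly a consequence of 12 eyes per arm and would apply to any binary outcome here, including complications.

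A reader might go further and infer that the yes/no result is close to uninformative, or that a finding of no difference is likely even if one technique clearly protects the cornea better. The documents do not support that. It requires that most eyes keep some staining after either operation, and the protocol gives no post-operative staining rate. Its eligibility criteria do not require reduced corneal sensation or long-standing exposure.

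Two further points are fair. The post-operative evaluation forms (Appendices 4 and 5) are illegible in the available text, so a grade or drawing on them cannot be excluded; the outcome definition would still be binary. And present/absent asks three assessors to agree on fewer boundaries than a grade does.

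What the reply does not remove is that change short of clearance goes unrecorded under the stated definition, and that a grade includes present/absent within it.

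**Conclusion.** The point holds as a matter of measurement. As defined, the only effectivity outcome that records corneal surface damage treats improvement or worsening short of clearance as no change, and this cannot be put right after data collection.

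Its size in power is uncertain. Under the assumed distributions the gain from grading at 12 eyes per arm runs from nothing (21% v 20%; 61% v 61%) to large (9% v 47%; 2% v 31%). Which applies depends on the true grade distributions, which the protocol does not give. The Fisher thresholds depend only on the number of eyes and on treating them as independent. Grading recovers information where the arms differ in severity, but it does not make 12 eyes per arm, or 15, adequate for this outcome. It is a worthwhile and cheap improvement to the design, not an internal contradiction in the plan.

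**What to change.** In Outcomes, item 3, replace the sentence that defines the scale with an ordinal staining grade that captures density as well as extent. Area alone would not do: dense and trace staining over the same region would share a grade. Have the three assessors agree the grade boundaries before the first subject is examined. Score the grade before surgery and at each follow-up visit, compare it by the Mann-Whitney test already listed under Statistical Methods, and keep present/absent as a summary derived from it.

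The cost is a sentence in the outcome definition, a field on the evaluation forms if they do not already have one, and a short agreement exercise. The dye, the examination and the assessors stay the same. The downside is some variation between assessors in grading, which prior agreement reduces but does not remove.
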